#### O-AS: to assess agoraphobic avoidance and distress

The Oxford Agoraphobic Avoidance Scale (O-AS)^49^ is an 8-item questionnaire assessing avoidance and associated distress. The scale has demonstrated good internal reliability, test–retest reliability, and validity.

#### OPDBQ: to assess safety-seeking behaviours and in situ-defences

The Oxford Paranoia Defence Behaviours Questionnaire (OPDBQ) is a newly developed questionnaire (Lambe et al., *in prep*) assessing avoidance in the past two weeks (Part 1; 12 items) and in situ-defences (Part 2; 20 items) which are strategies people use to keep themselves safe.

#### EofE: to assess access to alternative explanations

The Explanations of Experience (EofE) Interview [50] is a brief interview in which participants are asked to detail the key evidence they have in support of their main (distressing) belief. They are then asked: ‘Can you think of any other explanations for what you have described? Are there any other reasons, besides what you have said, that could possibly account for these experiences/ this evidence even if you think they are very unlikely?’ Alternative explanations are scored ‘Yes’ or ‘No’ indicating the presence/absence of flexibility.

#### FaST: to assess fast and slow thinking biases

The Fast and Slow Thinking (FaST) Questionnaire [51] is a 10-item self-report questionnaire assessing fast and slow thinking biases related to paranoid thoughts. The questionnaire involves 5-item assessing fast thinking and 5-item assessing slow thinking.

#### MADS-PM: to assess belief flexibility

The Maudsley Assessment of Delusions Schedule – Probability of Being Mistaken (MADS-PM) is a commonly used ‘Yes’ or ‘No’ item assessing whether people consider the possibility that they are being mistaken about their persecutory delusion [52].

#### QPR: to assess personal recovery

The 15-item questionnaire about the process of recovery (QPR) assesses personal recovery [53]. The QPR showed internal consistency, construct validity and reliability.

#### BRS: to assess resilience

The Brief Resilience Scale (BRS) is a 6-item questionnaire of resilience that was found to have good psychometric properties [54].

#### Qualitative interviews

Semi-structured qualitative interviews will be conducted with participants regarding their experiences with both therapies. The interviews that are conducted post-therapy will mainly focus on patients’ experiences with (1) collaborating with their therapist and peer counsellor (if Feeling Safe-NL) and effect on their recovery and (2) self-monitoring and visual feedback using the m-Path application. Interviews conducted 1-year after therapy completion will mainly focus on participants’ experiences with long-term recovery. Therapists and peer counsellors will also be interviewed after seeing several participants. The interviews will mainly focus on (1) their collaboration in the Feeling Safe-NL Programme and (2) using the m-Path application. Participants will be interviewed until saturation is achieved on all topics.

### Plans to promote participant retention and complete follow-up {18b}

This project team is committed to a recovery-oriented approach, and everyone working on the trial will be trained to ensure respectful and meaningful interactions with patients and community mental health staff. Trial assessors can visit participants at their local community mental health team or at their homes. Participants are also compensated for their time and travel. We also know from previous trials that patients remain motivated and generally like to contribute to this type of study [65]. Additionally, the Feeling Safe trial had high follow-up rates with less than 10% drop-out [5].

### Data management {19}

Questionnaire data (collected at 0-, 6-, 12-, and 18-month follow-up) will be collected in the Data Manager module of Research Manager in agreement with local mental healthcare institutions and VU University Amsterdam guidelines. Data from self-monitoring measures will be collected using the GDPR compliant platform m-Path of the KU Leuven (www.m-path.io). Audio recordings of the therapy sessions (for supervision and fidelity ratings) and qualitative interviews will also be stored in agreement with the VU University Amsterdam guidelines using the program Research Drive.

### Confidentiality {27}

Participants are given a research number (before randomization) and a randomization number (after randomization). No participant information is stored in the Research Manager. Participant information is kept on a separate and secured drive in a recruitment file with a password. This data is only accessible by the principal investigator, the project coordinator and trial assessors. In line with WMO guidelines, data will be stored for 15 years after the last intervention has been provided. We will save the key file about the participants for the entire period of 15 years for safety reasons.

### Plans for collection, laboratory evaluation and storage of biological specimens for genetic or molecular analysis in this trial/future use {33}

N/a. The trial involves an investigation of two psychological interventions using questionnaires and interviews.

## Statistical methods

### Statistical methods for primary and secondary outcomes {20a}

The primary continuous outcomes for mental wellbeing will be analyzed with linear mixed models (LMM) with outcome measurement (at the three follow-up timepoints) as the dependent variable and based on the intention-to-treat (ITT) principle. Baseline values will be added as covariates, time as a categorical variable, and treatment condition as a fixed effect. The regression coefficient of the LMM will be used as the between-group effect size (Feeling Safe-NL vs formulation-based CBTp) since this is the estimated difference in results between the groups.

The secondary continuous outcomes for the persecutory delusion, general paranoid ideation, patient-chosen therapy outcomes and activity will also be analyzed with LMM with outcome measurements (at the three follow-up timepoints) as the dependent variable and based on the intention-to-treat (ITT) principle. Baseline values will be added as covariates, time as a categorical variable, and treatment condition as a fixed effect. Between-group effect sizes (Feeling Safe-NL vs formulation-based CBTp) will be derived from the regression coefficient of the LMM. Outcomes for conviction of the main persecutory delusion (PSYRATS-DS) will also be dichotomized with recovery being defined as conviction falling below 50%. Logistic generalized estimating equations (GEE) with exchangeable correlation structure ITT analysis will be used to examine the effects on dichotomous outcomes, since GEE is reported to be a better estimator of effects in dichotomous outcomes than LMM [66]. Effects for Feeling Safe-NL vs formulation-based CBTp will be computed for “condition” (overall effect) and with interaction effects between time and condition for post-therapy (6-month follow-up; change during the treatment period) and for 12- and 18-month follow-up (change during the follow-up periods).

#### Mediation

We will also carry out parallel mediation analysis using the PROCESS macro for SPSS [67] to assess the effect of changes in maintenance factors of threat beliefs (e.g. worry, low self-esteem, anomalous experiences, insomnia, safety-seeking behaviours or defences, and trauma imagery), personal recovery and resilience on both mental wellbeing and severity of the persecutory delusion using the assessments at baseline, and 6 (post-therapy), 12- and 18-month follow-up. We will also assess whether the therapeutic relationship mediates changes from baseline to 6 months (post-therapy) and vise-versa.

Both (1) cost-effectiveness analysis (CEA) and (2) cost-utility analysis (CUA) will be conducted alongside the randomized trial. The outcome is Treatment Response (TR) defined as a clinically relevant change, in the CEA. In the CUA the outcome will be QALYs as estimated by the EQ-5D-5L using Dutch tariffs. Since we need to assign costs to meaningful outcomes, we use both QALYs and clinically relevant change defined using the primary outcome of mental wellbeing. For a clinically relevant change, we use Jacobson & Truax reliable change. For mental wellbeing measured with the WEMWBS, this corresponds to an improvement of 5 points. We calculated this as follows: SE means = 8.2 * square root (10.83) = 3.38; reliable change index: (2 × (3.38)^2^) = 5) of 5 points in WEMWBS mental wellbeing, based on studies on the WEMWBS and the Feeling Safe Trial [5, 28, 68]. Four types of costs will be considered: (1) intervention costs, (2) healthcare costs, (3) patients’ costs for making round trips to health services and for informal care, (4) costs stemming from productivity losses due to absenteeism and lesser efficiency while at work, both in paid and unpaid work. Costs, in Euros, will be estimated by multiplying units of health service (e.g. outpatient contacts, therapy sessions, hospital days) with their standard unit cost price as reported in the Dutch guideline for health economic evaluation indexed to the year 2022. The trial’s baseline balance between the Feeling Safe-NL and the formulation-based CBTp conditions will be assessed for both costs and outcomes and disbalances, if any, will be handled using appropriate regressions-based adjustments [69, 70]. Since the health economic follow-up at 18 months post-baseline does exceed 1 year, costs and effects will be discounted. Cumulative costs and health gains will be computed with the area under the curve method (or linear interpolation) to obtain cumulative estimates for costs, TR and QALY gains as accrued over the 18-month follow-up. The incremental cost-effectiveness ratio (ICER) will be computed to obtain the incremental costs per treatment responder and per QALY gained. To simultaneously evaluate both costs and outcomes, seemingly unrelated regression equations (SURE) models will be used. Because costs are usually non-normally distributed the SURE models will be bootstrapped (2500 times). Missing data will be imputed using predictive mean matching nested in nonparametric bootstraps of SURE models of costs and effects for intention-to-treat (ITT) analysis, as recommended by Brand and colleagues [71]. To visually present stochastic uncertainty, the bootstrapped ICERs will be plotted on the ICER plane. For decision-making purposes, the ICER acceptability curve will be plotted for various willingness-to-pay (WTP) ceilings for making judgments whether the Feel Safe-NL intervention offers good value for money relative to the formulation-based CBTp comparator condition. One-way sensitivity analyses directed at uncertainty in the main cost drivers (e.g. costs of hospital re-admissions) and outcomes (e.g. under different imputations) will be performed to assess the robustness of our findings. Both the analysis and reporting of the research findings will conform to the (extended) CONSORT and CHEERS-2022 statements [72].

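### The 5-point treatment-response threshold in the cost-effectiveness analysis is one standard error of the difference, not the Jacobson-Truax reliable change it is said to be (9.4 points on the plan's own inputs)

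*Protocol article*

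**What the plan says.** The health-economic paragraph of the protocol article (Statistical methods {20a}, directly after the mediation paragraph) sets the effect measure of the CEA: "The outcome is Treatment Response (TR) defined as a clinically relevant change, in the CEA". It names the method, "For a clinically relevant change, we use Jacobson & Truax reliable change", and gives the result: "For mental wellbeing measured with the WEMWBS, this corresponds to an improvement of 5 points".

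The working is printed in two steps. The first is "SE means = 8.2 * square root (10.83) = 3.38". The second begins "reliable change index: (2 × (3.38", squares that value and ends at 5. No multiplier and no confidence level appear in either step.

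The threshold then enters the result: "The incremental cost-effectiveness ratio (ICER) will be computed to obtain the incremental costs per treatment responder and per QALY gained". Response is also to be accumulated by the area-under-the-curve method, "to obtain cumulative estimates for costs, TR and QALY gains as accrued over the 18-month follow-up".

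Sensitivity analyses are planned for the main cost drivers and for "outcomes (e.g. under different imputations) will be performed to assess the robustness of our findings". No alternative response threshold is named.

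**The concern.** Reliable change in the Jacobson-Truax sense is meant to separate real change from measurement error. The observed change is divided by the standard error of the difference between two scores, and the ratio must exceed 1.96. The printed working appears to end at that standard error itself, so the denominator of the index has been taken as the threshold.

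Treatment response is the only effect measure of the CEA, and greater cost-effectiveness is a stated hypothesis (The Feeling Safe-NL Trial). A reader told that response means reliable change will assume that chance fluctuation has largely been excluded. If the threshold is about half the criterion, that assumption fails and the reported response rates describe something else.

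A smaller point sits in the same paragraph. A yes/no outcome accumulated as area under the curve is an amount of time in response, but the ICER is expressed per responder.

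**Working it through.** **Inputs** (all from the health-economic paragraph): SD 8.2; standard error of measurement (SEM) 3.38; stated threshold 5 points. Reliability is not legible as such. The printed 10.83 is read as 1 − 0.83 with the minus sign lost, because only that reading gives 3.38; taken literally, 8.2 × √10.83 = 26.99. The second step has likewise lost its root sign. Neither lost symbol is held against the plan.

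**Reproducing the plan's figure**

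1. SEM = SD × √(1 − reliability) = 8.2 × √0.17 = 3.38. This matches.
2. Standard error of the difference = √(2 × 3.38²) = √22.85 = 4.78, which rounds to the stated 5.

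The other candidates do not give 5: 2 × 3.38² without the root is 22.85; 1.96 × SEM is 6.63; 1.645 × 4.78 is 7.87 (carrying unrounded values).

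**Applying the named criterion**

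3. Threshold = 1.96 × 4.78 = 9.37 points, so 10 or more on a whole-point scale.
4. Reliable change index at 5 points = 5 / 4.78 = 1.05, against the required 1.96.
5. For 5 points to equal 1.96 standard errors with SD 8.2, reliability would have to be 1 − (5 / (1.96 × √2 × 8.2))² = 0.952. The plan's figures imply 0.83.

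**Chance of being called a responder with no true change** (normal error, one baseline-to-follow-up comparison, Φ the standard normal distribution function)

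| Rule | Calculation | Probability |
|---|---|---|
| Gain of 5 points, continuous | 1 − Φ(5 / 4.78) | 14.8% |
| 5 or more, whole points | 1 − Φ(4.5 / 4.78) | 17.3% |
| More than 5, whole points | 1 − Φ(5.5 / 4.78) | 12.5% |
| Gain of 9.37 points, continuous | 1 − Φ(9.37 / 4.78) | 2.5% |
| 10 or more, whole points | 1 − Φ(9.5 / 4.78) | 2.3% |

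**Illustration of the effect on the arms.** These values are assumed, not taken from the document: SD of change 8.2, mean change 5 points under CBTp, and 0.35 SD more under Feeling Safe-NL (5 + 0.35 × 8.2 = 7.87).

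| Threshold | CBTp | Feeling Safe-NL | Difference |
|---|---|---|---|
| 5 | 50% | 64% | 13.7 points |
| 9.4 | 30% | 43% | 13.0 points |

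**Area under the curve for a yes/no outcome.** With visits at 0, 6, 12 and 18 months, the trapezoid weights in years are 0.25, 0.5, 0.5 and 0.25, and response at baseline is zero by definition. Response at all three follow-ups gives 0.5 + 0.5 + 0.25 = 1.25; at 6 months only, 0.5; at 18 months only, 0.25. These are responder-years, not counts of responders.

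**The case against.** The arithmetic is hard to dispute: restoring the lost symbols does not help, because no calculation with a 1.96 factor in it ends at 5 on these inputs. The case on the other side concerns how much follows from it, and most of that case stands.

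- A reader might infer that most patients counted as responders would fail the cited criterion. The illustration says otherwise: 30/50 = 60% of CBTp responders and 43/64 = 67% of Feeling Safe-NL responders at 5 points also reach 9.4.
- A reader might infer that the cost per responder is badly distorted. The ICER uses the between-arm difference, and noise that inflates both arms largely cancels there. In the illustration the difference moves from 13.7 to 13.0 percentage points, about 5% of the ratio (13.7 / 13.0 = 1.05). Other assumptions could give more or less; the document does not settle it.
- Five points might be defensible on another basis. The paragraph also calls it clinically relevant and cites studies, which are not available here. As printed, though, those studies supply the inputs to the reliable-change calculation, and no separate justification is given. This keeps open the option of retaining 5, but not under the present label.
- The wording on planned sensitivity analyses of outcomes leaves room for another threshold. None is named, so this mitigates little.
- How response is accrued over time could be detail left to a fuller analysis plan. That is fair, so the area-under-the-curve point is secondary: a mismatch between two statements that needs a clarifying sentence. Requiring response to be judged at 18 months would be a preference, not a correction.

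**Conclusion.** The threshold is wrong as written for the method named. On the plan's own inputs Jacobson-Truax reliable change is 9.37 points (10 or more in whole points); the stated 5 is the standard error of the difference with the 1.96 multiplier omitted. This rests on one inference, that reliability is 0.83, which the printed SEM of 3.38 supports.

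The certain consequence is a mislabelled outcome with inflated response proportions in both arms. The figure of about 15% false responders is a model figure for patients with exactly zero true change; it is not a forecast of the share of observed responders who are false. The consequence for the incremental cost per responder is unknown and may be small.

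The reach is limited to the CEA. The primary and secondary mixed models use continuous scores, the cost-utility analysis uses QALYs, and the sample size does not depend on the threshold. Nothing in the document supports extending the concern to the primary conclusion. Severity: should-fix, because the error is clear and cheap to correct, and because a threshold changed after results are known would not be credible.

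**What to change.** Before unblinding, make one of two changes to the definition of treatment response:

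1. Keep the Jacobson-Truax definition and set the threshold at 1.96 × 4.78 = 9.4 points, stated as an improvement of 10 or more; or
2. Keep 5 points, drop the Jacobson-Truax label, state and justify another basis for 5, and pre-specify 10 or more as a sensitivity analysis.

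In either case print the formula in full, with the reliability and the multiplier.

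Separately, reconcile the accumulation of response with the ICER. Either keep the area under the curve and report cost per responder-year, or define responder status without it and report cost per responder.

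The cost is one corrected number or label and a few sentences. No data collection, sample size or primary analysis changes. Under option 1 the reported responder proportions will be lower in both arms. The article treats changes to outcomes and analyses as important modifications that go to the ethics committee (item 25), so the change should be recorded that way.

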### Outcomes {12}

The primary outcome will be psychological wellbeing (Warwick-Edinburgh Mental Well-Being Scale, WEMWBS)^28^ over time (assessed using the overall effect over time from baseline to 18-month follow-up and the effects at each timepoint) [27].

The secondary outcomes include persecutory delusion severity (Psychotic Symptom Rating Scale-Delusion Subscale, PSYRATS-DS) [42], general paranoid ideation (Revised-Green et al. Paranoid Thoughts Scale, R-GPTS), patient chosen outcomes (CHoice in Outcome In Cognitive behaviour therapy for psychosEs, CHOICE) and activity (time budget). Outcomes for conviction of the main persecutory delusion will also be dichotomized in line with the Feeling Safe Study (in which recovery is defined as conviction falling below 50%) [5].

We will also assess several mediators: trauma imagery (Trauma Screening Questionnaire, TSQ; PTSD Checklist for DSM-5, PCL-5) [43–45], insomnia (Insomnia Severity Index, ISI) [46], self-esteem (Brief Core Schema Scales, BCSS) [47], worry (Dunn Worry Questionnaire) [48], anomalous experiences (Voices Impact Scale, VIS; a publication concerning the psychometrics is underway), safety-seeking behaviours or defences (Oxford Agoraphobic Avoidance Scale, O-AS [49]; Oxford Paranoia Defence Behaviours Questionnaire, OPDBQ; Lambe et al., *in prep*), reasoning biases (Fast and Slow Thinking Questionnaire, FaST; Explanations of Experiences, EofE, Maudsley Assessment of Delusions Schedule-Possibility of being Mistaken, MADS-PM) [50–52], personal recovery (Questionnaire about the Process of Recovery, QPR) [53], and resilience (The Brief Resilience Scale, BRS) [54].

Other study parameters include the therapeutic relationship (Counsellor Rating Form-Short, CRF-S) [55] and working alliance (Working Alliance Inventory-Short Form Revised, WAI-SR) [56]. For the health-economic evaluation we will use the Treatment Inventory of Costs in Patients with psychiatric disorders (TIC-P) and the standardized EuroQol  5-Dimension 5-Level questionnaire (EQ-5D-5L) at baseline and after 6 (post-intervention) 12 and 18 months.

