### Sample size {14}

The sample size for longitudinal intention-to-treat (ITT) analyses with linear mixed models (LMM) was calculated according to the method presented by Liu and Liang (1997) and based on data from previous RCTs [5, 13–15, 24]. Although an ITT analysis with LMM is robust against moderate attrition, we aim to include an additional 10% to compensate for potential dropout. With alpha = 0.05; beta = 0.2; rho = 0.5; 3 repeated follow-up assessments and 10% drop-out; we will need 95 participants in each arm to detect small to medium effects (0.35). Therefore, we aim to include 190 participants.

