#### TIC-P and EQ-5D-5L: to assess resource use and quality-adjusted life years

Resource use will be measured with the Trimbos Institute and iMTA Cost Questionnaire for Psychiatry (TIC-P), short version. Using the TIC-P, we will measure healthcare usage, patients’ and their family’s out-of-pocket costs, and productivity losses owing to absenteeism and presenteeism. The EuroQol 5-dimension 5-level questionnaire (EQ-5D-5L) will be used to measure health-related quality of life (HRQoL). The EQ-5D-5L describes health states over five domains of mobility, self-care, usual activities, pain/discomfort, and anxiety/ depression. Dutch tariffs [62] will be applied to each of the health states to obtain utilities, in which 0 represents death and 1 full health. Next, utilities will be combined over time by calculating the area under the curve (or linear interpolation) to calculate quality-adjusted life years (QALYs).

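### The economic evaluation adjusts for baseline utility and costs only if an imbalance is judged present, although baseline utility is part of every QALY; adjustment should be unconditional

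*Protocol article*

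**What the plan says.** The health-economic text follows the Mediation paragraph under Statistical methods {20a}. It says that baseline balance between the arms "will be assessed for both costs and outcomes and disbalances, if any, will be handled using appropriate regressions-based adjustments". It gives no criterion for an imbalance and names no baseline covariate for the bootstrapped SURE models that estimate costs and effects.

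The section on the TIC-P and EQ-5D-5L builds QALYs so that "utilities will be combined over time by calculating the area under the curve". Outcomes {12} sets both instruments "at baseline and after 6 (post-intervention) 12 and 18 months", so the baseline utility is the first point of the curve.

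For the continuous clinical outcomes, {20a} states an unconditional rule: "Baseline values will be added as covariates, time as a categorical variable, and treatment condition as a fixed effect".

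**The concern.** A pre-randomisation value sits inside the outcome. A chance difference in baseline utility reaches the incremental QALY in two ways: directly, through its share of the area, and indirectly, because patients with a higher utility at baseline tend to have a higher utility later. Both happen whether or not anyone calls the difference an imbalance.

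Under the stated rule, whether this is corrected depends on an undefined judgement made with the baseline data in hand. Two analysts could reach different models from the same data. If the check is made once, outside the bootstrap, the acceptability curve will also leave out the uncertainty from choosing the model; the article does not say where the check is made. Cost-effectiveness is a stated hypothesis of the trial, so the choice matters.

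**Working it through.** **The plan's own figure.** The article gives no variance or power for QALYs, costs or the ICER. The figure that can be reproduced is the sample size, whose inputs are "With alpha = 0.05; beta = 0.2; rho = 0.5; 3 repeated follow-up assessments and 10% drop-out" and an effect of 0.35. Taking alpha as two-sided (the side is not stated):

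n per arm = 2(1.960 + 0.842)² × [(1 + 2×0.5)/3] / 0.35² = 85.4, and 85.4/0.9 = 94.9, so 95.

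This confirms that 0.5 is the repeated-measures correlation in use. It was given for the clinical sample size. Applying it to EQ-5D-5L utilities is my assumption, so a range is shown.

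**Weights.** Linear interpolation over 0, 6, 12 and 18 months gives w = (0.25, 0.5, 0.5, 0.25) years, total 1.5. Baseline carries 0.25/1.5 = 1/6.

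**Never adjusted against always adjusted.** Take utilities with unit variance and the same correlation ρ between all visits. The squared weights sum to 0.625.

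- Var(QALY) = 0.625(1 − ρ) + 2.25ρ
- Cov(QALY, baseline) = 0.25 + 1.25ρ, which is also the slope on baseline utility
- Adjusted variance = Var − Cov²

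At ρ = 0.5: Var = 0.3125 + 1.125 = 1.4375; Cov = 0.875; adjusted variance = 1.4375 − 0.7656 = 0.672; ratio = 1.4375/0.672 = 2.14.

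| ρ | Exchangeable: variance, slope, adjusted variance | Ratio | Ratio if correlation decays with time, AR(1) |
|---|---|---|---|
| 0.3 | 1.112, 0.625, 0.722 | 1.54 | 1.27 |
| 0.5 | 1.438, 0.875, 0.672 | 2.14 | 1.52 |
| 0.7 | 1.762, 1.125, 0.497 | 3.55 | 2.16 |

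The article discounts effects but gives no rate. With assumed rates of 1.5% or 4%, the ratio at exchangeable 0.5 stays at 2.14 to 2.15.

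**The conditional rule.** The table compares two fixed rules, and the protocol states neither. So the rule of adjusting only when baseline utility differs was simulated (10,000 trials per setting, exchangeable correlation, 85 and 95 per arm). The triggers are assumptions. Variance of the QALY difference relative to always adjusting:

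| ρ | Trigger p<0.05 | Trigger p<0.20 |
|---|---|---|
| 0.3 | about 1.4 | about 1.2 |
| 0.5 | about 1.8 | about 1.4 |
| 0.7 | about 2.9 | about 1.9 |

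With p<0.05 the adjustment is made in about 5% of trials.

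**Size of an uncorrected chance difference.** The standard error of the baseline difference at 95 per arm is √(2/95) = 0.145 SD. Multiplied by slopes of 0.625, 0.875 and 1.125, one standard error shifts the incremental QALY by 0.091, 0.127 and 0.163 SD-years. With an assumed utility SD of 0.25 that is 0.023, 0.032 and 0.041 QALYs; it scales in proportion to the SD. Under a 5% trigger, baseline differences up to 1.96 × 0.145 = 0.28 SD stay uncorrected.

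**An alternative reading.** The article also speaks of QALY gains. If that means the area minus 1.5 times baseline utility, the variance is 2.125(1 − ρ). Against always adjusting, the ratio is 2.06, 1.58 and 1.28 at ρ = 0.3, 0.5 and 0.7. Subtraction over-corrects and does not replace the covariate.

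**The case against.** The strongest points on the other side, and what stands of each:

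- **The article does plan adjustment.** True, so the ratios for never adjusting are an upper reference. If any observed difference counted as an imbalance, adjustment would be nearly universal and the ratio would approach 1. The wording allows that reading but does not fix it.
- **No test is named.** Also true. The p-value triggers above are mine. What the text does fix is that the choice depends on the data.
- **Covariate lists belong in a SAP or health-economic plan.** A missing list would not be a finding in a condensed article. The article goes further, though: it states a conditional rule. An unseen SAP may already replace it.
- **The clinical contrast is incomplete.** The unconditional rule is stated for the continuous outcomes. No baseline covariate is named for the logistic GEE analysis, and treatment response is likewise dichotomous. The contrast holds for QALYs, which are continuous.
- **The inputs are assumed.** The utility correlation and SD are not in the document. With decaying correlation, a doubling of variance needs a ρ near 0.7.

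A reader might infer that the ICER itself carries about twice the variance it needs. The documents do not support that. The cost per QALY also depends on cost variance, whose baseline correlation is not given, and the cost per treatment responder contains no utility. A reader might also infer bias. Randomisation keeps the unadjusted QALY difference unbiased on average.

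**Conclusion.** The point holds as one of precision and analytic discretion in the economic evaluation; the primary outcome analysis is not affected. Adjusting only when an imbalance is perceived, without a criterion, leaves unflagged chance differences in the QALY and lets the model follow the data.

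For the incremental QALY, never adjusting costs about 1.3 to 3.5 times the variance of always adjusting, for assumed correlations of 0.3 to 0.7 and two correlation shapes (2.1 at exchangeable 0.5, 1.5 with decay). A conditional rule recovers part of this: at exchangeable 0.5 the excess is about 1.8 times with a p<0.05 trigger and about 1.4 times with p<0.20. No corresponding figure can be given for costs or for either ICER.

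**What to change.** State that every bootstrapped SURE model includes baseline EQ-5D-5L utility in the QALY equation and baseline costs in the cost equation, regardless of observed balance. Keep the balance check as description only. Because SURE lets each equation have its own covariates, the modelling approach need not change.

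Site as a covariate, and baseline WEMWBS in the treatment-response equation, are optional and not needed for this point.

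The cost is one or two sentences in the SAP or health-economic analysis plan, before the data are analysed. Both instruments are already scheduled at baseline, so nothing more is collected. If the SAP already prespecifies this, only the article's sentence needs to be marked as superseded.

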### Participant timeline {13}

Following enrolment, participants will be allocated to formulation-based CBTp or the Feeling Safe-NL Programme. Assessments will be carried out at baseline and after 6 (post-intervention) 12 and 18 months. A schematic diagram is provided in Table 1.

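### The CEA integrates a yes/no Treatment Response over time but labels the resulting ratio as cost per responder; the quantity computed is time in response

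*Protocol article*

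**What the plan says.** All the relevant statements but two are in the health-economic paragraph of the protocol's Statistical methods section, printed after Mediation.

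- Effect measure: "The outcome is Treatment Response (TR) defined as a clinically relevant change, in the CEA". For the WEMWBS, "this corresponds to an improvement of 5 points".
- Accumulation: costs and health gains are computed by area under the curve, or linear interpolation, "to obtain cumulative estimates for costs, TR and QALY gains as accrued over the 18-month follow-up". TR is named alongside costs and QALYs.
- Ratio: the next sentence says that the ICER is computed "to obtain the incremental costs per treatment responder and per QALY gained".
- Discounting: "costs and effects will be discounted". No rate is given.

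Elsewhere, Participant timeline {13} gives the measurement times: "Assessments will be carried out at baseline and after 6 (post-intervention) 12 and 18 months". The section on the TIC-P and EQ-5D-5L uses the same integration for QALYs: "utilities will be combined over time by calculating the area under the curve".

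**The concern.** Integrating utilities over time is the normal route to QALYs, because a QALY is utility multiplied by time. TR is different. A threshold on change from baseline makes it a yes/no status at each visit. Integrating that status also multiplies by time, so the result is in years (or, if divided by follow-up, an average proportion of time) spent in response. The protocol attaches a per-responder label to it.

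The label matters for how the result is used. The protocol plans acceptability curves over a range of willingness-to-pay ceilings. A ceiling per additional responder and a ceiling per additional year in response are different amounts of money for different things. A reader who takes the label at face value would set the wrong one against the curve.

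**Working it through.** **Inputs.** Visits at 0, 0.5, 1.0 and 1.5 years (Participant timeline {13}). TR is coded 1 if the WEMWBS has improved by at least 5 points from baseline and 0 otherwise; this coding is implied by the threshold and by the word responder, and is not written out. TR is 0 at baseline, since change from baseline is zero there. Discounting is ignored because no rate is given; it would alter the later weights but not the unit.

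**The plan's own figure.** The only stated number here is the 5-point threshold. It reproduces as 8.2 × √(1 − 0.83) = 3.38 and √(2 × 3.38²) = 4.78, about 5, if the printed 10.83 and the absent outer root are printing or extraction losses. The protocol states no cost per responder to reproduce.

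**AUC of TR by the trapezoid rule.**

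AUC = 0.25 × (0 + TR6) + 0.25 × (TR6 + TR12) + 0.25 × (TR12 + TR18) = 0.5 × TR6 + 0.5 × TR12 + 0.25 × TR18 (years)

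| Response at 6 / 12 / 18 months | AUC (years) | AUC ÷ 1.5 |
|---|---|---|
| no / no / yes | 0.25 | 0.17 |
| yes / no / no | 0.50 | 0.33 |
| no / yes / no | 0.50 | 0.33 |
| no / yes / yes | 0.75 | 0.50 |
| yes / no / yes | 0.75 | 0.50 |
| yes / yes / no | 1.00 | 0.67 |
| yes / yes / yes | 1.25 | 0.83 |

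Only one pattern equals 1 in years, and it belongs to someone who is no longer a responder at 18 months. After division by 1.5 no pattern equals 1.

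**Effect on the ratio.** The 18-month responder difference is used below purely as a yardstick. For any incremental cost, the AUC-based ratio divided by the cost per 18-month responder is (responder difference at 18 months) ÷ (AUC difference). Suppose one arm has 10 percentage points more responders:

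- at every visit: AUC difference 0.10 × 1.25 = 0.125, factor 0.10 / 0.125 = 0.8. After division by 1.5 the difference is 0.083 and the factor 1.2.
- at 18 months only: 0.10 × 0.25 = 0.025, factor 4. After division by 1.5, factor 6.
- at 6 months only: 0.10 × 0.5 = 0.05, with no additional responder at 18 months, so the per-responder ratio is undefined.

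With assumed response rates at 6/12/18 months:

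| Arm 1 vs arm 2 (%) | AUC difference (years) | Responder difference at 18 months | Factor |
|---|---|---|---|
| 50/50/50 vs 35/35/35 | 0.1875 | 0.15 | 0.80 |
| 55/45/40 vs 35/35/35 | 0.1625 | 0.05 | 0.31 |
| 35/42/50 vs 35/35/35 | 0.0725 | 0.15 | 2.07 |
| 55/45/35 vs 30/35/40 | 0.1625 | −0.05 | opposite sign |

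As an example in money, an assumed incremental cost of EUR 2,000 in the second row gives 2,000 / 0.1625 = EUR 12,308 per year in response, against 2,000 / 0.05 = EUR 40,000 per 18-month responder.

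**The case against.** The strongest reply is that a time-integrated response is a sensible effect measure for this trial. The primary objective is the overall effect over time from baseline to 18 months as well as the effect at each visit, and the cost-effectiveness hypothesis covers the same period. Nothing in the protocol makes 18-month status the target. This stands: time in response is legitimate, and the fault lies only in calling it responders. For the same reason the factors above measure how far two quantities differ, not how wrong one of them is.

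It can also be said that this is a condensed article, that 0/1 coding is not spelled out, and that TR may have slipped into a sentence meant for costs and QALYs. The absence of a counting visit would indeed be no finding by itself. But here two stated sentences disagree. If TR is a status at each visit, the stated method yields time in response. If TR is a single endpoint status, the AUC does not apply to it. Either way one sentence has to change.

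Several stronger readings are tempting and are not supported:

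- That the AUC rewards transient over sustained response. It does not: response at all visits scores 1.25, more than any other pattern. What is true is narrower: response at 6 and 12 months and then lost (1.00) outscores response at 12 and 18 months (0.75).
- That the ratio is biased in a known direction. A constant difference makes it 20% lower in years and 20% higher after division by 1.5, and the protocol does not say which scale is used.
- That the 5-point threshold needs correcting. The point does not depend on it.
- That baseline costs contaminate the 18-month total. This would need cost reports to be interpolated from baseline, which the text does not spell out.

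**Conclusion.** The point holds as a mismatch between method and label. Followed as written, the CEA denominator is time in response, while the ratio is described as per responder. In the illustrations with a positive responder difference at 18 months, the two ratios differ by a factor of between 0.31 and 4 on the scale of years; they can also differ in sign, or one can be undefined. These factors rest on assumed response rates, 0/1 coding, no discounting, and 18-month status as the yardstick. The weights 0.5, 0.5 and 0.25 follow from the visit schedule and the stated method.

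The consequence is confined to the CEA ratio and any acceptability curve drawn for it. The QALY-based CUA and the mixed-model analysis of the primary outcome do not use this quantity.

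**What to change.** Choose one of two wordings and fix it before the analysis, so that the choice cannot follow the observed pattern of response:

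1. Keep the AUC for TR, state its scale (years, or proportion of follow-up), and relabel the ratio and its acceptability curve accordingly, for example as cost per year in response.
2. Count responder status at one pre-specified visit (18 months is one option), keep the per-responder label, and reserve the AUC for QALYs.

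The first uses the 6- and 12-month response data; the second is simpler to read but discards them. Both need only a change of wording in the health-economic plan. No new data, visits or participants are required.
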